**Methods:**

A four-armed household, cluster-randomized, controlled study will be conducted to assess the combined impact of HS, LLINs and push-pull agricultural technology (PPT) against clinical malaria in children in Ethiopia. The unit of randomization will be the household, which includes a house and its occupants. A total of 838 households will be enrolled in this study. In this trial 246 households will receive LLINs and HS, 250 will receive LLINs, HS and PPT, 175 households will receive LLINs and PPT. The remaining 167 houses which receive LLINs only will be used as control. One child aged ≤14 years will be enrolled per household in each treatment and followed for clinical malaria using active case detection to estimate malaria incidence for two malaria transmission seasons.

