### Sample size rationale

#### Sample size of houses for screening

Studies conducted in Ethiopia [12] and The Gambia [9, 10, 18, 36] have suggested that houses with their doors and windows screened can result in reduction of mosquito density measured between 40 to 70% as compared to control houses. In addition to mosquito proofing, house screening has proved to be effective intervention in reducing malaria incidence. Studies conducted to evaluate the impact of housing improvement on odds of malaria infection showed varying degree of efficacy. Tusting et al., [22], reviewed 53 published papers on housing and malaria interaction and reported 47% lower odds of malaria infection in ‘modern houses’ as compared to ‘traditional houses’. In Ethiopia, the protective efficacy of house screening was evaluated on 46 randomly selected households in Arba-Minch Zuria for 6 months and 61% reduction of malaria case was documented in screened houses as compared to the control houses [23]. In Kenya, malaria incidence was followed up in 80 screened houses for a year and 100% case reduction was reported [37]. Thus, considering the experiences from other countries and malaria prevalence information from the study area, this design is developed to measure the impact of house screening. A study conducted by Ayalew et al., (2016) [34] in 3 villages *(Kebeles)* in the district showed a 2.8% malaria prevalence and used as a benchmark for this trial. Accordingly, 838 households, will be selected from 30 villages *(Kebeles)*, using 80% power at the 5% significance level.

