**Fig. 1 Fig1:**
[figure not shown]
Flow chart of the study

In this study, a total of 167, 246, 250 and 175 houses will be included in four different treatments, treatment 1 (control, LLINs only), treatment 2 (LLINs and HS), treatment 3 (LLINs, HS and PPT) and treatment 4 (LLINs and PPT), respectively. The differences in sample size across arms is due to differences in number of households within each sub-village. To full fill the total sample size, we did the random selection based on population size of each sub-village. Census of children under 14, and above 14 years of age will be made in all 838 households selected. One child will be randomly selected from each house for annual malaria parasite survey. In addition to the annual parasite screening survey, monthly follow up will be implemented in all households to monitor clinical malaria by health extension workers. If a child moves or quits the study, we will replace the child from the same house. In instances where the whole family leaves the area, we will document them as lost to follow up.

The selected children will be checked up every month for clinical symptoms of malaria infection, splenomegaly, and development of anaemia. Blood test will be conducted if the child develops clinical symptoms. The child will also be surveyed at the beginning and end of each transmission season to estimate the prevalence of *Plasmodium species* infection, parasite density, and the prevalence of anaemia. Collections will be made from both indoor and outdoor settings.

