### Study endpoints/outcomes

#### Clinical evaluations

The main outcomes of the clinical study will be the malaria incidence, splenomegaly, and anaemia. Thus, the baseline clinical survey of all study children will take place between Sept and Oct 2020 to determine the clinical parameters. As part of the follow up, starting from Nov 2020, trained health extension workers will visit the house of each child and take data of clinical symptoms, temperature, and splenomegaly (sign of spleen enlargement). While monthly follow up of the child continues throughout the 2 years of study period (Sept 2020 to Dec 2022) for documentation of any malaria incidence, blood testing of the entire cohort of the study children will be repeated at the end of each rainy season (Sept/Oct 2021) and Sept/Oct 2022). In between the annual clinical surveys (i.e., at the time of monthly follow up), blood testing will be done only to children who develop fever to minimize community fatigue development. Temperature measurement, RDT testing, blood haemoglobin measurement, blood sample collection for microscopy will be conducted by a licensed laboratory professional following the WHO guideline [44].

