### Statistical methods

#### Malaria incidence data analysis

Change in clinical malaria incidence over 2 years period among the treatment and control arms will be determined using Poisson distribution. In this trial we will follow modified ITT protocol and if a child is lost from follow up, or withdraw from the study, or refuse to be included in the treatment, it will be immediately replaced by a child from the reserve list. The Relative Risk (RR) and RR Reductions (RRR) will be calculated with corresponding 95% confidence intervals to compare dichotomous variables, and difference in means will be used for additional analysis of continuous variables. Mixed effects Poisson model will be used to test the difference in incidence rates among the study arms, to determine effects of the repeated measurements within house, village, the effect of year and village-intervention interaction effects. To control the effect of clustering or village and individual level confounding factors such as gender and age, these covariates will be fitted in to random effects during analysis. If a child is diagnosed with malaria case within 28 days of the first episode with the same plasmodium species, then it will be put on treatment as part of the safety protocol, however, the case will not be included in the analysis. The prevalence of anaemia among the study participants (children) will be analysed using the guideline developed by world health organization [47]. Accordingly, all children between 6 and 59 months of age, whose Hb level is recorded between 10.0–10.9 g/dl, 8.0–9.9 g/dl and less than 8.0 g/dl will be graded as mild, moderate, and severe, respectively. In line with this we will also report community level anaemia prevalence. Thus, a prevalence of anaemia will be stated as severe if it is documented over 40% (combining mild, moderate, and severe) and moderate if the prevalence is 20–39.9%. Both malaria and anaemia prevalence data will be compared in the intervention and control houses using multilevel mixed-effects logistic regression models, taking village effects into account.

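### The logistic models for malaria and anaemia prevalence name only village effects, although the same children are surveyed repeatedly; if rounds are pooled without a child or house level, the arm comparisons are anti-conservative

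*Protocol article*

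**What the plan says.** All places are in the Protocol article.

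- **Prevalence and anaemia model** (Malaria incidence data analysis): both outcomes are compared between intervention and control houses "using multilevel mixed-effects logistic regression models, taking village effects into account".
- **Incidence model** (same section): a mixed-effects Poisson model is used "to determine effects of the repeated measurements within house, village, the effect of year and village-intervention interaction effects".
- **Survey rounds, first account** (Clinical evaluations): "the baseline clinical survey of all study children will take place between Sept and Oct 2020", and then "blood testing of the entire cohort of the study children will be repeated at the end of each rainy season", dated Sept/Oct 2021 and Sept/Oct 2022. Between these surveys only febrile children have blood taken.
- **Survey rounds, second account** (Study flow chart): "The child will also be surveyed at the beginning and end of each transmission season to estimate the prevalence". The abstract's Methods paragraph gives two transmission seasons.
- **One child per house** (Study flow chart): "One child will be randomly selected from each house for annual malaria parasite survey".

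Anaemia is listed among the main clinical outcomes (Clinical evaluations). Parasite infection and anaemia are both in specific objective i.

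**The concern.** The article gives two models in one section. The incidence model has a structure for repeated measurement. The prevalence model does not, although its data are also repeated on the same child.

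A village intercept does not repair this. With 838 children in 30 villages it is shared by about 838/30 ≈ 28 children, so it cannot absorb the correlation between one child's own results. A child's arm does not change between rounds, whether allocation is by household (abstract) or by sub-village (Sequence generation). Any within-child correlation therefore passes in full into the variance of the arm comparison.

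If rounds are stacked in the model as named, two results from one child count as two independent results. An arm difference in a main clinical outcome could then be declared significant on overstated precision.

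**Working it through.** **The plan's own figure.** The only relevant figure is the nominal level: "838 households, will be selected from 30 villages *(Kebeles)*, using 80% power at the 5% significance level". Sidedness is not stated, and two-sided is assumed here. The article gives no false-positive rate for this model and no within-child correlation, so there is nothing further to reproduce. The formula below returns 5% at zero correlation, as it should.

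**Inputs**
- Rounds pooled per child, m. Clinical evaluations gives 2 after baseline, or 3 if the baseline survey is counted as an outcome round. Study flow chart gives start and end of two seasons, 2 × 2 = 4.
- Within-child correlation, rho. This is an assumption, shown from 0.1 to 0.7.
- No further clustering by sub-village, so that this source is isolated.

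**Formulas**
- Design effect: DE = 1 + (m − 1) × rho
- True standard error / reported standard error = √DE
- True false-positive rate = 2 × [1 − Φ(1.96/√DE)]

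**Two follow-up rounds (m = 2)**

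| rho | DE | √DE | 1.96/√DE | true rate |
|---|---|---|---|---|
| 0.1 | 1.1 | 1.049 | 1.869 | 6.2% |
| 0.3 | 1.3 | 1.140 | 1.719 | 8.6% |
| 0.5 | 1.5 | 1.225 | 1.600 | 11.0% |
| 0.7 | 1.7 | 1.304 | 1.503 | 13.3% |

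**If more rounds were pooled**

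| m | rho 0.1 | rho 0.3 | rho 0.5 | rho 0.7 |
|---|---|---|---|---|
| 3 | 7.4% | 12.1% | 16.6% | 20.6% |
| 4 | 8.6% | 15.5% | 21.5% | 26.6% |

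**Simulation check.** Under no arm effect, 167 children were compared with 246 across 30 villages. The test was a village-stratified Mantel-Haenszel test that ignored the child, with 4,000 runs per setting. For m = 2:

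| rho | prevalence 2.8% | prevalence 30% (assumed) |
|---|---|---|
| 0 | 5.0% | 4.8% |
| 0.1 | 5.7% | 6.3% |
| 0.3 | 8.1% | 8.8% |
| 0.5 | 11.3% | 11.8% |
| 0.7 | 14.2% | 13.4% |

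This agrees with the formula. It stands in for the planned mixed-effects logistic model and is not a run of that model.

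**One round at a time.** With one child per house, m = 1 and DE = 1, so there is no inflation from this source.

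**The case against.** The strongest reply is that the article describes neither pooling nor a village-only model. It calls the models multilevel, which does not exclude a child or house level. Prevalence is naturally estimated survey by survey, and Epidemiological data collection methods speaks of an annual survey. Details of random effects may also sit in an analysis plan that is not shown. All of this stands, and it makes the point conditional. It does not remove the contrast within one section, where repetition is named for incidence and only village for prevalence. Nor does the article name a single survey as the one that counts.

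A reader might infer from the tables that the false-positive rate simply rises to 9–27%. The documents do not support that reading:
- It takes pooling as given.
- It takes rho as 0.3–0.7 for both outcomes. For Plasmodium infection, with a 2.8% benchmark prevalence (Sample size of houses for screening) and treatment of every detected positive (Epidemiological data collection methods), a low value such as 0.1 is more plausible.
- Its upper end needs four rounds. These rest on one sentence under Study flow chart, which conflicts with the annual surveys described elsewhere and with febrile-only testing between them.

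It would also be too much to say that 838 children are counted as 838 × 2 = 1,676 independent anaemia results. The anaemia grades are defined only for ages 6–59 months, while objective i concerns ages 5 to 14, so the number contributing is unclear.

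**Conclusion.** The concern holds in conditional form. The structure named for the prevalence and anaemia models does not match the repeated surveys of one cohort, and it is narrower than the structure given for incidence.

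If the two follow-up rounds under Clinical evaluations are pooled without a child or house level, the nominal 5% test runs at about 6% for rho 0.1 and about 9–13% for rho 0.3–0.7. The lower figure suits treated infection and the higher range suits anaemia, whose status is more likely to persist within a child. Larger rates require more pooled rounds than Clinical evaluations provides after baseline.

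The result rests on an assumed rho, a common correlation between rounds, and complete follow-up. Analysing each round separately removes this inflation. It would, however, leave several tests with none designated as the main one.

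**What to change.** In Malaria incidence data analysis, adopt one of the following:

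1. Give the prevalence and anaemia logistic models a random intercept for child or household and a fixed effect of survey round, in addition to the area-level effects, as is already done in kind for incidence. A household intercept is workable because there is one study child per house and Study flow chart replaces a departing child from the same house.
2. Name one survey, for example end-of-season 2022, as the confirmatory comparison with one observation per child, and report the other rounds as supportive.

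In either case, reconcile Clinical evaluations and Study flow chart on the number of whole-cohort surveys, and say whether the baseline round enters as an outcome.

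The change takes a sentence or two and needs no new data. Its cost is somewhat wider, correct confidence intervals. Under option 1 the odds ratios become conditional on the child or household. At the benchmark prevalence only about 838 × 0.028 ≈ 23 children would be positive per round, so the intercept variance for infection may be poorly estimated. Option 2 avoids that difficulty.

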### Entomological data analysis

Indoor and outdoor *Anopheles* densities will be compared for each study arm using a student t-test. Overall mosquito density among treatment arms will be compared using one-way analysis of variance (ANOVA) and if there is significance difference among treatment arms mean separation test will be done using turkey’s range test. The sporozoite rate will be determined as the proportion of malaria vectors positive for CSPs over the total number tested for CSPs.

The durability test of screening material will be conducted following the guideline developed by Kinde et al. (2018) [23] and modification of world health organization [48] guideline for evaluation of durability of long-lasting insecticidal mosquito nets under operational conditions. Accordingly, the durability of the screening intervention will be measured by assessing the number of holes on the meshes. Fabric integrity of all HSs fixed into windows and doors will be assessed for holes at each monitoring round. The proportion of HSs with any holes will be presented with total number of HSs in surveyed households as denominator. The scale of HS damage will be quantified using hole index formula recommended for mosquito nets and it is given as Hole index = (A x no. of size-1 holes) + (B x no. of size-2 holes) + (C x no. of size-3 holes) + (D x no. size-4 holes). Numbers 1, 2, 3, 4 refer to the size of the whole, letters A, B, C, D refer to the weight of the hole and given as 1, 23, 196 and 578 [48]. The fabric integrity of screens fixed in doors will be analysed separately as its exposure to wear and tear is higher as compared to that of windows. In depth interviews, photo-based observation will be conducted to measure community acceptance of the intervention.

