## Methods

### Study setting and period

This study will take place between September 2020 and December 2022 in the Jabi-Tehnan district of Amhara regional state, Northwest Ethiopia. The capital town is Finote-Selam, which is about 387 km from the National capital, Addis Ababa, and 176 km Southwest of the regional capital, Bahir Dar. The population of the district was 211,516 in 2017 with an average annual growth rate of 2.8% [32]. The district is divided into 38 villages *(Kebeles),* which is the lowest administrative unit of the country, and three town administrations. More than 90% of the people in the district live in rural areas practicing mixed farming.

The altitude of the district ranges from 900 to 2300 m above sea level. Much of the area lies in the higher altitude range, closer to 2300 m. Agro-ecologically, 88% of the district is classified as mid land and the remaining 12% as low land. The topography of the district is dominated by areas of flat plain. According to Asmare & Gure, 2019 [33], the topography is classified as 65% flat plain, 15% mountainous, 15% undulating and 5% valley. The rainfall distribution is uni-modal, and the rainy season normally lasts for 4 months from mid-May to mid-September. The annual rainfall ranges 1250 mm per annum. The mean minimum and maximum temperatures are 14 °C and 32 °C, respectively [33]. According to the report compiled from 17 villages *(Kebeles)* of the district, malaria is a major health problem threat resulting in total mortality of 4345, and average Plasmodium annual parasite rate (API) of 11% ([name] 2018, personal communication). A cross sectional active malaria prevalence survey from randomly selected kebeles of the district in 2013 showed the disease prevalence of 2.8% [34]. According to the preliminary information collected from the district, houses are made of walls plastered with mud and roofs covered with corrugated iron sheet. According to the baseline survey conducted in the area 59% of the respondents reported that they keep the livestock in the same house but in separate rooms [35].

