#### Sample size of houses for entomological data collection

According to WHO guideline for malaria entomology [38], a representative sample size for entomological collections per village will be 10 houses. Thus, a total of 40 houses (10 houses per treatment arm) will be used for mosquito collection. The treatment households are dispersed over three different geographical zones (low land, mid-land, and high land). Therefore, 40 households will be randomly selected for each geographical zone. Thus, a grand total of 120 houses will be selected for sampling mosquitoes from all three zones.

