### Randomization

As the study area is composed of different localities (and elevations) of the district, the risk of malaria infection also varies among *kebeles* (document review from district malaria information). Therefore, the study area will be first clustered into *kebeles* and then each kebele will be clustered in to *sub-kebeles*. The randomization process will be conducted using the STATA’s *sampsi* package and using *sub-kebele* as a unit of randomization. Efforts will be made to ensure that each *kebele* receives balanced number of treatments following the standard protocol developed by Pinder et al. (2016) [14]. Stratified randomization by *sub-kebeles* will take out the kebele effect and the likelihood of chance imbalances between study arms. All entomological, epidemiological, and social studies will be conducted following the same rule described above i.e., stratified randomization. The randomization will be done by ZA to prevent selection bias by concealing the allocation sequence from the field researchers assigning sub-kebeles into the four treatment arms until the moment of assignment. Thus, both the chief investigator and the principal investigator will not be involved in the randomization process.

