### Entomological data collection methods

A total of 10 houses, (five houses for indoor and five houses for outdoor LTs) catches will be selected from each study village. Indoor and outdoor catches will be collected from each study arm. Mosquitoes will be collected indoor and outdoor from 6:00 pm to 06:00 am from each selected house using standard battery-operated CDC light traps. Traps will be hung from the ceiling or from roof support at the foot end of the bed where people sleep at night and each trap will be suspended about 1.5 m from the floor. Traps will be also hung outdoor under the eaves of the house for outdoor mosquito collection. Each trap will be set by trained research team members. Collection bags will be retrieved from traps in each house in the morning between 06:00 am and 07:00 am. All unfed, fed, half gravid and gravid adult female *Anopheles* mosquitoes (Indoor and Outdoor) will be identified using taxonomic keys of Gilles and Coetzee (1987) [42]. Dried head and thorax of *Anopheles gambiae* s.l., and *Anopheles pharoensis* collected by CDC light traps from each study villages *(Kebeles)* will be carefully separated from the abdomen and tested for *P. falciparum* and, *P. vivax-210 and P. vivax-247* circumsporozoite proteins (CSPs) simultaneously following the protocol developed by Beier et al. 1988 [43]. On agricultural pest assessment, the severity of infestation will be scored on visual observation of the foliar damage attributed to each pest using a 1 to 5 scale, where 1 is clean with no visual infestation symptoms, 2 = very little damage, 3 = high level of damage where plants show the presence of FAW larvae feeding and most of the young leaves show infestation symptom, 4 = severe damage where almost 75% of the leaves are severely affected and excrement is visible on the infested areas and the maize whorls, and 5 = very severe damage where total plant damage due to FAW is visible.

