### Entomological evaluations (medical entomology)

The major entomological outcomes of the study are changes in mosquito densities, rates of mosquito infection (sporozoite rates), and the entomological inoculation rate (EIR). Both indoor and outdoor mosquito collections will be made using the Centres for Disease Control (CDC) light traps to estimate the mosquito density. Collections will be made twice per year (July to Sept and January to March) starting from July 2020 to Oct 2022. All mosquito collections will be preserved in silica gel and transported to the International Centre of Insect Physiology and Ecology (ICIPE) Kenya, Nairobi, ICIPE molecular laboratory, where they will be identified to species level and examined for sporozoite infection using Polymerase chain reaction (PCR) technique. Blood meal analysis of fed females will be done using Enzyme linked immunosorbent assays (ELISA).

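### The one-way ANOVA and Tukey comparison of mosquito density between arms ignores repeated collections and sub-kebele allocation, so its error rate is not the nominal 5%

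*Protocol article*

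**What the plan says.** All references are to the protocol article.

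- **Outcome.** Entomological evaluations (medical entomology): "The major entomological outcomes of the study are changes in mosquito densities", together with sporozoite rates and the entomological inoculation rate.
- **Arm comparison.** Entomological data analysis: "Overall mosquito density among treatment arms will be compared using one-way analysis of variance (ANOVA", with Tukey's test if the overall result is significant. No random effect, cluster adjustment, repeated-measures term, count distribution or transformation is mentioned.
- **Indoor versus outdoor.** Same section: indoor and outdoor "densities will be compared for each study arm using a student t-test".
- **Repeats.** Entomological evaluations (medical entomology): "Collections will be made twice per year", from July 2020 to October 2022. Handling of dropouts/withdrawals substitutes a reserve house when a family leaves, which implies that the same houses are otherwise followed.
- **Allocation.** Sequence generation and Randomization make the sub-kebele the unit, with 66 of them; the sequence is concealed from the field researchers "assigning sub-kebeles into the four treatment arms until the moment of assignment". Randomization adds that the entomological study follows the same rule. The Abstract and Study flow chart instead describe allocation to households, the latter with the village as block.
- **Sample.** Sample size of houses for entomological data collection: "a grand total of 120 houses will be selected for sampling mosquitoes from all three zones".
- **Contrast.** Malaria incidence data analysis plans a mixed-effects Poisson model for incidence, with repeats within house and village, and multilevel logistic models for malaria and anaemia prevalence.

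**The concern.** A one-way ANOVA takes every observation as independent. Catches from one house in successive rounds share that house's construction, occupants and distance from breeding sites. Houses in one sub-kebele share local ecology, and if the sub-kebele is what was allocated, they share the arm too. Differences between houses or sub-kebeles then enter the arm means, but the residual mean square does not reflect them properly. The F test and the Tukey contrasts therefore need not hold their stated level.

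The stakes are material. Reduced mosquito entry is how house screening is meant to work, indoor vector density is a named end point in the Abstract, and the second specific objective compares mosquito exposure inside houses with nets alone. The protocol recognises this dependence for malaria but not for mosquitoes collected under the same allocation. Because the method is stated, this is more than a detail left to an analysis plan.

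**Working it through.** **Inputs from the protocol**

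- Houses: 10 per arm × 4 arms = 40 per zone; 40 × 3 zones = 120, which reproduces the stated total. 120 / 4 = 30 per arm. With the five-indoor, five-outdoor split under Entomological data collection methods, 15 per arm carry indoor traps.
- Rounds: July–September 2020, January–March 2021, July–September 2021, January–March 2022, July–September 2022 = 5. The timeline table marks entomological collection in every month from January to November of 2021 and 2022, so five is a reading, not a stated count.
- Sub-kebeles: 66 / 4 = 16.5 per arm at most. The number sampled for mosquitoes is not given.
- Level: 5%, stated for the main sample size and assumed here.

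**Assumptions not in the protocol**

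Negative binomial counts with dispersion k = 0.5; mean 2 per trap (15-house runs) or 3 (30-house runs); log-normal house and sub-kebele effects with the standard deviations (SD) shown; no arm effect. Count = Poisson(mean × exp(sub-kebele effect + house effect) × gamma noise), tested by one-way ANOVA over four arms.

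**Check 1. Overdispersion without clustering.** Rejection is 5.0% (30 houses, one round), 4.6% (30 houses, five rounds) and about 5% (15 houses, five rounds). Skewed counts alone do not inflate the error here.

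**Check 2. 15 houses per arm, five rounds, 2,000 trials per setting.** Ranges cover repeated runs with different seeds.

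| House log-SD | Sub-kebele log-SD | Trap-nights | House means |
|---|---|---|---|
| 0.5 | 0 | 10–12% | 4% |
| 0.8 | 0 | 19–20% | 3–4% |
| 0.8 | 0.4 (3 per arm) | 32–34% | 9–10% |

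**Check 3. 30 houses per arm, five rounds, 3,000 trials per setting.**

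| Sub-kebeles per arm | Sub-kebele / house log-SD | Trap-nights | House means | Sub-kebele means |
|---|---|---|---|---|
| none | 0 / 0.5 | 12.1% | 4.5% | – |
| none | 0 / 1.0 | 24.2% | 3.9% | – |
| 16 | 0.3 / 0.3 | 13.7% | 6.3% | 4.6% |
| 16 | 0.5 / 0.5 | 24.9% | 7.9% | 4.3% |
| 16 | 1.0 / 0.5 | 43.7% | 11.3% | 3.9% |
| 6 | 0.3 / 0.3 | 25.3% | 16.1% | 4.5% |
| 6 | 0.5 / 0.5 | 45.9% | 23.4% | 4.2% |
| 6 | 1.0 / 0.5 | 74.8% | 45.7% | 3.5% |

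Making the sub-kebele the unit of analysis restores the level in every clustered setting.

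**Check 4. Zone and season effects balanced over arms but left out of the ANOVA.** Zone effects are ±1 and season effects ±0.7 on the log scale (assumed), with 30 houses per arm.

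| Setting (sub-kebele / house log-SD) | Trap-nights | House means |
|---|---|---|
| Zone; 0.5 / 0.5; 5 sub-kebeles per zone and arm | 22.2% | 2.7% |
| Zone and season; 0.5 / 0.5; 5 | 14.5% | 2.4% |
| Zone and season; 0.3 / 0.3; 5 | 7.1% | 1.1% |
| Zone and season; 0 / 0.5 | 5.6% | 0.9% |
| Zone and season; 0 / 0 | 1.8% | 0.3% |
| Zone; 0.5 / 0.5; 2 sub-kebeles per zone and arm | 40.4% | 11.6% |

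Omitted balanced effects swell the residual and pull rejection down, sometimes well below 5%.

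**The case against.** Several points on the other side stand and limit the finding.

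- **Unit of analysis.** The text speaks of density and does not say whether trap-nights or house averages are compared. With house averages, repeats in a house no longer inflate the error, and only sub-kebele clustering can.
- **Direction.** Check 4 shows that the planned test can be conservative. A reader might infer that it always declares far too many differences; the documents do not support that.
- **Randomization unit.** If households were allocated within villages, the sub-kebele part would not inflate the arm test. The repeated-house part would remain for trap-night data (12% to 24% in Check 3, 5.6% in the matching Check 4 setting).
- **Cause.** It is tempting to blame many zeros and long tails. Check 1 shows otherwise. A count model is still the better description, but for the effect measure and its interval.
- **The t-test.** It compares indoor with outdoor traps within an arm, so it cannot produce false differences between arms. Its own error rate was not examined here.
- **House numbers.** Entomological data collection methods says that ten houses for "catches will be selected from each study village". A reader might multiply by 30 villages, get 300, and see a contradiction with 120. That follows only if all 30 kebeles are meant; 12 entomology villages of ten houses give 120.
- **Zones.** Study setting and period says "88% of the district is classified as mid land and the remaining 12% as low land", which names no high land, while the mosquito sample uses three zones. One is an agro-ecological classification and the other is called geographical, and altitude runs from 900 to 2300 m. This needs clearer wording and is not evidence against the ANOVA.

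**Conclusion.** The point holds in this form: the stated arm comparison of mosquito density leaves out the repeated collections and the sub-kebele, so its real error rate is not the nominal 5%. The defect can be read from the text; its size cannot. Across the assumed settings without omitted zone or season effects, trap-night ANOVA rejects in 10% to 34% of null trials with 15 houses per arm and in up to 75% with 30 houses and six sub-kebeles per arm. House-mean ANOVA gives about 4% without sub-kebele effects and roughly 6% to 46% with them. With large balanced zone and season effects omitted, rejection falls and can drop below 5%.

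These figures rest on assumed variance components, a five-round reading of the schedule, an unstated number of sampled sub-kebeles and an unstated unit of analysis. The sub-kebele component also depends on resolving the conflict over the randomization unit. The change should be made because the outcome is a major one and the remedy is cheap.

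**What to change.** 1. Replace the ANOVA and Tukey arm comparison with a negative binomial mixed model of count per trap-night. Use fixed effects for arm, indoor/outdoor, arm by location, round and zone, and for the kebele stratum where estimable, with random intercepts for house and sub-kebele. Report density ratios against control with 95% confidence intervals and multiplicity-adjusted arm contrasts. The indoor-versus-outdoor comparison can come from the same model.
2. This model was not simulated here. Analysis of sub-kebele means, which held 3.5% to 4.6% in Check 3, is a simple sensitivity check.
3. Reconcile the Abstract and Study flow chart with Sequence generation and Randomization on the allocation unit.
4. Separately, say which villages count as study villages for mosquito collection so that the number agrees with 120 houses, and how the three zones relate to the mid-land and low-land split.

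Cost: slightly more analysis work and usually wider intervals. No new data are needed.
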